## Abstract

**Background:**

Recent functional magnetic resonance imaging (fMRI) evidence suggests that pre-supplementary motor area (pre-SMA) activity supports language recovery in post-stroke aphasia (PSA). As a key hub within domain-general cognitive networks, the pre-SMA represents a promising target for individualized neuromodulation. While intermittent theta burst stimulation (iTBS) can enhance language recovery, its efficacy may be limited by generalized targeting strategies.

**Objective:**

This study aims to investigate the efficacy of fMRI-guided, neuronavigated iTBS targeting the individualized pre-SMA for promoting language recovery in subacute PSA and to elucidate its underlying neural mechanisms via functional connectivity (FC) analysis.

**Methods:**

In this single-center, randomized, double-blind, sham-controlled trial, 40 participants with early subacute PSA (1–3 months post-stroke) are allocated to receive either active or sham iTBS targeting the left or right pre-SMA, localized via individualized MRI mapping. Participants will undergo a 2-week intervention, with language and neuroimaging assessments conducted at baseline, immediately post-intervention, and at a 1-month follow-up. Primary outcome measures are the Western Aphasia Battery (WAB). Second outcomes measures will be including the Boston Naming Test (BNT), the Boston Diagnostic Aphasia Examination (BDAE), non-language cognitive assessment (NLCA), alongside functional connectivity analysis from resting-state fMRI.

**Expected outcomes:**

We anticipate that this trial demonstrates the efficacy of individualized pre-SMA iTBS in improving language recovery in PSA. Furthermore, we expect to identify treatment-induced neuroplastic changes in functional and structural brain connectivity. The findings could establish a novel precision neuromodulation approach for aphasia rehabilitation by identifying patient-specific biomarkers of treatment response.

**Clinical trial registration:**

https://www.chictr.org.cn/, ChiCTR2500108996.

## Introduction

Post-stroke aphasia (PSA) affects around 30% of stroke survivors and is frequently associated with enduring language impairments that significantly diminish quality of life and elevate healthcare burdens (1). These deficits spanning spontaneous speech, comprehension, repetition, and naming, not only hinder daily communication but also impair rehabilitation progress and long-term outcomes (2, 3). Speech and language therapy (SLT) remains the standard intervention for PSA, its benefits are often modest (SMD = 0.28) (1). Noninvasive brain stimulation techniques, particularly repetitive transcranial magnetic stimulation (rTMS), emerge as promising adjuncts for enhancing language recovery in PSA (2, 4, 5). The intermittent theta burst stimulation (iTBS), a specific rTMS protocol, offers unique advantages through its ability to induce an increase in cortical excitability with shorter treatment durations (6, 7).

Optimizing stimulation targets is critical for maximizing the therapeutic benefits of rTMS. Although traditional approaches have focused on perisylvian language—related areas, including inferior frontal gyrus (IFG) and superior temporal gyrus (STG) (8, 9), growing evidence highlights the importance of domain-general networks involving aphasia recovery (10, 11). Such domain-general regions underpin various cognitive processes, including working memory, reasoning, attention, and executive function (12). The cingulo-opercular network, a key domain-general network consisting of the dorsal anterior cingulate cortex, pre-supplementary motor area (pre-SMA), anterior insula, and inferior frontal gyrus, is implicated in post-stroke language recovery (12–14).

Recent neuroimaging studies reveal that the pre-SMA shows compensatory activation in patients with PSA, particularly those with left temporo-parietal and frontal infarctions (10, 15–17). This activation pattern correlates with improved performance on language tasks including picture description and naming, and serves as an independent predictor of recovery outcomes alongside traditional prognostic factors like age and aphasia severity (10, 18, 19). Functionally, the pre-SMA contributes to multiple language-related processes including speech initiation, verb generation, and auditory-motor integration (20–23). Beyond its domain-general cognitive functions, the pre-SMA is also deeply integrated within motor planning and execution circuits, forming a key interface between motor and language systems. Recent evidence suggests that language processing benefits from motor and motor-imagery training, supporting the embodied language framework (24–26). This dual role highlights that targeting pre-SMA may facilitate language recovery not only through cognitive control but also via motor-related reorganization. Nevertheless, our current protocol focuses primarily on the language-related mechanisms of pre-SMA activity, consistent with our recent finding demonstrating its association with post-stroke speech recovery (27). Anatomically, the pre-SMA's vascular supply from the bilateral anterior cerebral arteries often preserves its structural integrity in aphasia patients with left middle cerebral artery infarction (28), making it particularly suitable as a neuromodulation target in PSA patients. These converging lines of evidence strongly support the therapeutical potential of pre-SMA as a neuromodulation target for promoting language recovery after stroke. While recent work has shown that iTBS applied to the superior frontal gyrus (encompassing the pre-SMA) can improve language function in PSA patients (8), the neuroplastic mechanisms underlying these behavioral gains remain poorly understood.

Traditional rTMS approaches often employ standardized anatomical targeting based on group-level brain templates, which fails to accommodate individual variability in functional neuroanatomy and connectivity patterns. This limitation is particularly salient in prefrontal regions like the pre-SMA, where intersubject variability in both location and connectivity profiles can substantially diminish treatment efficacy (29). To tackle this challenge, we develop a personalized brain functional sector (pBFS) framework. This approach integrates resting-state functional magnetic resonance imaging (fMRI) with DTI to produce connectivity maps tailored to each individual. This method identifies precise localization of each patient's pre-SMA region based on their unique structural and functional connectivity (FC) patterns, thereby optimizing stimulation targeting (30, 31). The clinical potential of such individualized rTMS protocols has already been demonstrated in depression, schizophrenia, and neurodegenerative diseases, where connectivity-guided stimulation may serve as a promising tool for improving treatment response compared with conventional approaches (32, 33). Emerging evidence further supports the effectiveness of rTMS guided by individualized functional or structural connectivity for specific symptom management, with studies in healthy individuals further demonstrating its precision in targeting specific brain networks (34–37).

Our personalized targeting strategy aligns with the bimodal balance–recovery model of post-stroke rehabilitation (38). This framework proposes that functional recovery mechanisms are determined by the degree of structural reserve in the damaged hemisphere. When substantial white matter integrity is preserved (high structural reserve), recovery primarily occurs through remodeling of ipsilesional networks (interhemispheric competition model). Conversely, when structural damage is severe (low structural reserve), compensation predominantly relies on contralesional hemisphere recruitment (compensatory model). To operationalize this model clinically, we employ DTI to quantify the structural integrity of the left frontal aslant tract (FAT), thereby guiding individualized decisions to target either the ipsilesional or contralesional pre-SMA. Moreover, this trial specifically focuses on the early subacute phase (1–3 months post-stroke), which is recognized as a critical window for neuroplasticity and recovery. During this period, beneficial disinhibition and reorganization processes occur within motor and language networks, facilitating experience-dependent cortical remapping and responsiveness to neuromodulation (39–41). Selecting this time window is therefore intended to maximize the potential efficacy of individualized pre-SMA stimulation.

The current study has two primary objectives: (1) to determine whether fMRI-guided, individualized pre-SMA iTBS enhances language recovery in subacute PSA compared to sham stimulation, and (2) to characterize the neuroplastic mechanisms of treatment effects by examining pre-SMA-related circuit reorganization and functional connectivity changes within language network and domain-general cognitive networks. Our findings may establish a new precision medicine paradigm for aphasia rehabilitation that integrates connectivity-based targeting with biologically informed treatment protocols.

## Methods

### Trial design

This investigation is designed as a prospective randomized controlled trial conducted at a single center, with a double-blind, sham-controlled structure. In total, 40 individuals with subacute PSA are enrolled from Wuxi Central Rehabilitation Hospital. The ethics approval number is WXMHCIRB2025LLky116, and the clinical registry number is ChiCTR2500108996. Participants are randomly allocated at a 1:1 ratio to either the real stimulation group or the sham stimulation group. Assessments are conducted on the enrollment day (T0) and following the completion of the iTBS intervention (T1), aphasia test batteries and fMRI are performed to evaluate language functions in PSA. Figure 1 illustrates the study design and data collection procedures, while Table 1 summarizes the timeline of enrolment and assessments.

**Figure 1 F1:**
[figure not shown]
Study design and data collection.

**Table 1 T1:** Timeline of enrolment and assessments.

**Time-point**	**Screening and allocation**	**Post-randomization**		**Follow-up**
	**Day** −**7**~−**1**	**Day 0**	**Day 14 (**±**3 day)**	**Day 44 (**±**3 day)**
**Enrolment**				
Eligibility screening	√			
Informed consent	√			
Medical history	√			
Randomization	√			
MRI scanning		√	√	
**Assessment**				
NIHSS		√		
WAB		√	√	√
BDAE		√	√	√
BNT		√	√	√
NLCA		√	√	√

NIHSS, National Institute of Health Stroke Scale; WAB, Western Aphasia Battery; BDAE, Boston Diagnostic Aphasia Examination; BNT, Boston Naming Test; NLCA, non-language-based cognitive assessment.

### Participants and recruitment

Participants will be recruited from Wuxi Central Rehabilitation Hospital. Eligibility requires meeting all of the following items: (1) a confirmed diagnosis of aphasia secondary to ischaemic stroke, with symptoms lasting between 1 and 3 months; (2) left-hemisphere ischaemic stroke confirmed by brain CT or MRI scan; (3) a first-ever stroke with a single lesion; (4) Aphasia Quotient (AQ) on the WAB < 93.8; (5) aged between 50 and 75 years; (6) native Mandarin speakers with at least primary school education; (7) right-handedness; (8) intact premorbid language function; (9) informed about the procedures of iTBS treatment and brain imaging scans, and provided written informed consent.

Given the focus of the current protocol, only patients with non-fluent aphasia (as classified by the WAB) will be included. The aphasia type of all enrolled participants will be determined and documented at baseline to ensure diagnostic accuracy and sample homogeneity.

Exclusion criteria include: (1) severe auditory, visual, or cognitive deficits limiting compliance; (2) significant dysarthria (NIHSS item 10 ≥ 2); (3) impaired consciousness (NIHSS item 1a ≥ 1); (4) major psychiatric disorders such as severe depression or anxiety that may interfere with participation; (5) aphasia due to other causes (e.g., brain tumor, traumatic brain injury, Parkinson's disease, motor neuron disease); (6) history of epilepsy or substance abuse; (7) contraindications to TMS or fMRI (e.g., scalp lesions, defects of the skull, intracranial implants, pacemakers, or drug pumps).

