### Randomization

Participants will be randomly allocated in a 1:1 ratio to either the active iTBS or sham group. Randomization will be stratified by aphasia subtype (non-fluent only) to maintain balanced group allocation. The allocation sequence will be safeguarded through the use of consecutively numbered, sealed opaque envelopes, which are prepared and kept by personnel independent of the trial. Prior to the intervention, an independent researcher (not blinded) will open the corresponding envelope to determine and confirm each participant's group allocation.

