### Lesion delineation and quantification

Stroke lesions were manually delineated on T2-weighted MRI images using MRIcron (https://www.nitrc.org/projects/mricron) by two trained raters and verified by a senior neuroradiologist. Lesion masks were normalized to MNI space to calculate lesion volume and the lesion–tract overlap ratio with the left frontal aslant tract (FAT). Both indices were included as covariates in statistical analyses to control for lesion-related effects.

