## Data analysis

### Behavioral data

Repeated-measures ANOVAs are used to assess changes in WAB, BNT, NLCA scores, and speech parameters, with phase (pre- vs. post-treatment) as a within-subject factor and group (active vs. sham iTBS) as a between-subject factor. *Post hoc* comparisons are adjusted using the Bonferroni method. Data normality is checked with the Kolmogorov–Smirnov test; non-normally distributed variables are analyzed using the Wilcoxon signed-rank test. An intention-to-treat (ITT) approach is applied in the presence of missing data.

In cases where the assumptions of normality or homogeneity of variances are violated, a non-parametric Aligned Rank Transform (ART) ANOVA was applied to test for main and interaction effects. This approach preserves the interpretability of ANOVA-type models while providing robustness to deviations from normality. For *post-hoc* comparisons, the Wilcoxon signed-rank test (within-group) and Mann–Whitney *U*-test (between-group) are used with Bonferroni correction.

To further explore variability in treatment response, a sub-analysis will be performed within the non-fluent aphasia cohort, stratifying participants according to their baseline WAB-AQ scores to examine severity-related differences in iTBS efficacy. Participants will be categorized into mild (WAB-AQ: 50.4–93.7), moderate (30.1–50.3), and severe (0–30) aphasia groups based on their baseline scores (55). Changes in primary behavioral outcomes (WAB, BNT, NLCA) will be compared across these severity strata using mixed-design ANOVAs, followed by Bonferroni-corrected *post hoc* tests. This analysis aims to explore potential differential treatment responses across varying degrees of language impairment.

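### Time since stroke spans 1 to 3 months at entry but is neither balanced at randomisation nor adjusted for, which may cost precision in the WAB-AQ comparison without making it invalid

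*Protocol article*

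**What the plan says.** - **Entry window.** Under Participants and recruitment, patients qualify "with symptoms lasting between 1 and 3 months". The Introduction justifies the choice by describing the "early subacute phase (1–3 months post-stroke), which is recognized as a critical window for neuroplasticity and recovery".
- **Randomisation.** "Randomization will be stratified by aphasia subtype (non-fluent only) to maintain balanced group allocation". Participants and recruitment admits only non-fluent patients, so this factor has one level.
- **Primary model.** Behavioral data specifies repeated-measures ANOVAs for WAB, BNT and NLCA, "with phase (pre- vs. post-treatment) as a within-subject factor and group (active vs. sham iTBS) as a between-subject factor". Table 1 puts the post-treatment assessment at day 14 (±3).
- **Covariates.** The only ones named are lesion volume and the overlap of the lesion with the left frontal aslant tract, under Lesion delineation and quantification: "Both indices were included as covariates in statistical analyses to control for lesion-related effects".
- **Sub-analysis.** The exploratory analysis works by "stratifying participants according to their baseline WAB-AQ scores to examine severity-related differences in iTBS efficacy". It uses severity, not time since stroke.

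**The concern.** With two phases, the group x phase test compares the arms on change over about two weeks. Taking differences within a patient removes stable differences in level but not differences in the rate of recovery. If patients treated at one month are recovering faster than patients treated at three months, that variation stays in the error term of a comparison between 32 to 40 people. The arms may also differ by chance in their position in the window, and the stated model has no term that would allow for this.

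Stroke timing must be established for every participant to confirm eligibility, so the information is already held. Baseline AQ and lesion size do not record it. Two patients with the same AQ, one at one month and one at three, may have different amounts of recovery ahead; this is reasoning and not a figure from the documents.

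**Working it through.** The plan gives no figure on this point, so there is none to reproduce. The group sizes are 16 evaluable and 20 enrolled per arm (Sample size estimation; 16/(1 - 0.2) = 20).

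**1. Size of chance imbalance.** Assumption: entry uniform over 30 to 90 days, simple 1:1 allocation.

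- SD of time since stroke = 60/√12 = 17.3 days.
- SE of the arm difference = 17.3 × √(2/n) = 5.5 days at n = 20 per arm and 6.1 days at n = 16.
- 95% range = ±1.96 × SE = ±11 days (n = 20) and ±12 days (n = 16).
- P(difference > 7 days): 7/5.48 = 1.28, giving about 20%; 7/6.12 = 1.14, giving about 25%. Simulation gave 20% and 25%.

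**2. What an imbalance does to the estimate.** A one-SE imbalance at 20 per arm is √(2/20) = 0.32 SD of time since stroke. If time since stroke explains a share R² of outcome variance, the unadjusted difference moves by 0.32 × √R² outcome SD: 0.07, 0.10, 0.14 and 0.17 for R² of 5%, 10%, 20% and 30%. Over repeated randomisations this movement averages to zero, and the usual standard error already includes it.

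**3. Gain from adjusting.** Let ρ be the partial correlation of time since stroke with T1 AQ given baseline AQ. It is not in the documents. With N the total sample size,

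net gain = 1 / [(1 - ρ²)(1 + 1/(N - 5))] - 1.

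| Assumed ρ | N = 40 | N = 32 |
|---|---|---|
| 0 | -3% | -4% |
| 0.1 | -2% | -3% |
| 0.2 | 1% | 0% |
| 0.3 | 7% | 6% |
| 0.4 | 16% | 15% |
| 0.5 | 30% | 29% |

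Break-even is where ρ² = 1/(N - 4): √(1/36) = 0.17 at N = 40 and √(1/28) = 0.19 at N = 32. The variance penalty at ρ = 0 is 1/35 = 2.9% and 1/27 = 3.7%. Counting the two lesion covariates as well replaces N - 5 by N - 7, so the penalty becomes 1/33 = 3.0% and 1/25 = 4.0%; the picture does not change.

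**4. Where the covariate must enter.** With complete pre and post scores, the group x phase estimate is the difference between arms in mean (post - pre). A covariate that is constant within a patient and enters only as a main effect adds the same amount to both scores and cancels. In simulated complete data with n = 40, the interaction estimate was identical with and without such a term, and changed only when covariate x phase was added. The gains in step 3 are those of an ANCOVA of the T1 score. In the repeated-measures model with covariate x phase, the relevant correlation is the one with change.

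**The case against.** The strongest reply is that this is an omission from a condensed article, and that covariates are often settled in the full protocol or SAP. The lesion section limits its two indices to lesion-related effects and does not say that the list is closed. That stands in part: a fuller document may name more covariates. But this article does set out the stratum, the model and two covariates, and the suggestion is a concrete improvement to what it sets out.

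Second, the documents do not show that recovery differs within the window. The Introduction treats 1 to 3 months as one period, and where it names established prognostic factors it gives age and aphasia severity. This stands. Restricting entry to two months also already limits the factor, and under the uniform assumption arm means lie within a week of each other in about 80% of trials at 20 per arm. The benefit is therefore possible, not demonstrated.

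Third, a reader might infer that chance imbalance in recovery stage biases the iTBS effect or undermines the test. The documents do not support that. Allocation is randomised 1:1, so the unadjusted estimate is unbiased, its error rate holds, and its standard error already covers such imbalance.

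**Conclusion.** The point holds as a possible loss of precision that is cheap to address; it is a minor improvement. Time since stroke varies across a period the protocol itself describes as one of recovery, and it is neither balanced by design nor included in the model. The validity of the primary comparison is not in question. What is missing is a correction, given the allocation that actually occurs, for a difference between arms in time since stroke.

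The size depends on a prognostic strength that the documents do not give. Below a partial correlation of about 0.17 (0.19 at n = 32) adjustment loses slightly, at 0.2 to 0.3 the gain is small, and only at 0.4 to 0.5 does it become material. The imbalance figures rest on uniform entry over 30 to 90 days. It would also go too far to read the article as showing that time since stroke is a strong predictor here.

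**What to change.** Before unblinding, pre-specify days from stroke to enrolment as a continuous covariate for WAB-AQ, and likewise for BNT and NLCA, in one of two forms:

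- an ANCOVA of the T1 score on group, baseline score, lesion volume, tract overlap and days since stroke; or
- the stated repeated-measures model with a days-since-stroke x phase term. The lesion indices need the same interaction if they are to affect the group x phase estimate.

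Report the distribution of days since stroke by arm. The randomisation need not change.

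The cost is a sentence or two in the analysis section, no new data, and one degree of freedom: about 3-4% more variance if time since stroke turns out to be unrelated to outcome.

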**Figure 2 F2:**
[figure not shown]
Personalised stimulation target localisation protocol. This figure illustrates the process of localising personalised TMS targets for language rehabilitation.

The FAT's fractional anisotropy (FA) will evaluate bilaterally. The FA ratio between the affected and unaffected sides was defined as relative FA (rFA, rFA = FAipsilesional/FAcontralesional), following the method used to evaluate the corticobulbar tract (CBT) in stroke recovery (45). As defined in prior studies, an rFA > 0.5 indicates high integrity, while an rFA ≤ 0.5 indicates low integrity. It should be noted that the specific rFA threshold for defining a functionally intact FAT has not been established in the literature. Therefore, we have extrapolated from studies on other major tracts, such as the corticospinal tract (CST) and CBT, in which an rFA > 0.5 correlates with preserved motor and swallowing function (45–47). Participants with high FAT integrity receive stimulation over the ipsilesional pre-SMA, while those with disrupted FATs are stimulated over the contralesional pre-SMA.

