### fMRI preprocessing and functional connectivity analysis

The resting-state fMRI data are preprocessed using Statistical Parametric Mapping (SPM8; http://www.fil.ion.ucl.ac.uk/spm) and the Data Processing Assistant for Resting-State fMRI [DPARSF; (56)]. Preprocessing of the fMRI data involved the following steps: (1) discarding the first 10 volumes to allow signal stabilization and participant adaptation, leaving 190 images for analysis; (2) correcting for slice timing and head motion, with all participants exhibiting less than 2 mm displacement and 2° rotation; (3) co-registering T1-weighted images to the mean functional image and segmenting into gray matter, white matter, and cerebrospinal fluid; (4) regressing out confounding signals, including motion parameters and BOLD signals from ventricles and white matter; (5) normalizing functional images to MNI space using segmentation parameters (57), and resampling to 3-mm isotropic voxels; (6) smoothing with a 6-mm FWHM Gaussian kernel; and (7) applying temporal band-pass filtering (0.01–0.08 Hz) to remove low-frequency drift and high-frequency noise.

After the preprocessing, functional connectivity (FC) maps are calculated by computing Pearson correlation coefficients between the mean time series of each seed and all brain voxels, followed by conversion to Fisher *z*-values. Seed regions are defined as 6-mm-radius spheres centered at the ipsilesional pre-SMA (*x* = −4, *y* = 8, *z* = 50) and contralesional pre-SMA (*x* = 4, *y* = 8, *z* = 50), based on previous studies (10).

FC changes are analyzed at the voxel level using a 2 × 2 mixed-design repeated-measures ANOVA, with group (active vs. sham) as a between-subject factor and time (pre- vs. post-treatment) as a within-subject factor. Voxel-wise multiple comparisons are corrected using the false discovery rate (FDR, *p* < 0.05, cluster-level). *Post hoc* analyses further examine FC alterations within the pre-SMA–language network. Correlation analyses between FC changes and behavioral improvements are performed using Pearson correlation coefficients, with *p*-values FDR-corrected for multiple comparisons (*p* < 0.05).

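### No stated step checks whether the infarct overlaps the pre-SMA target or the fixed ipsilesional connectivity seed, although eligibility does not limit lesion site

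*Protocol article*

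**What the plan says.** **Eligibility** (Protocol article, Participants and recruitment). Lesion site is described by two items: "left-hemisphere ischaemic stroke confirmed by brain CT or MRI scan" and "a first-ever stroke with a single lesion". A further restriction is behavioural: "only patients with non-fluent aphasia (as classified by the WAB) will be included". No exclusion criterion names an arterial territory or a relation between lesion and target.

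**Rationale** (Introduction). Among several arguments for the target, the protocol says that the blood supply of the pre-SMA from the anterior cerebral arteries "often preserves its structural integrity in aphasia patients with left middle cerebral artery infarction".

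**Side of stimulation** (Personalized stimulation target localization, text under Figure 2). The ratio of ipsilesional to contralesional FAT FA is cut at 0.5: "an rFA > 0.5 indicates high integrity, while an rFA ≤ 0.5 indicates low integrity". Then: "Participants with high FAT integrity receive stimulation over the ipsilesional pre-SMA, while those with disrupted FATs are stimulated over the contralesional pre-SMA".

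**Connectivity analysis** (fMRI preprocessing and functional connectivity analysis). "Seed regions are defined as 6-mm-radius spheres centered at the ipsilesional pre-SMA" at x = −4, y = 8, z = 50, with a mirror seed at x = 4. No lesion check on either seed is stated.

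**Use of the lesion data** (Lesion delineation and quantification). Lesions are drawn on T2 images and normalised to MNI space. Lesion volume and lesion–FAT overlap enter the analyses as covariates.

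**The concern.** The only argument in the Introduction that the target tissue survives the stroke is made for middle cerebral artery infarction, and there only as something that often happens. Enrolment is not confined to that territory. A patient with a left medial-frontal infarct and non-fluent aphasia can therefore meet the lesion criteria.

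Two things are at stake:

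- **The target.** Active stimulation over infarcted cortex is not a fair test of personalised pre-SMA iTBS and would pull the treatment effect towards zero.
- **The seed.** The second primary objective is about reorganisation of pre-SMA circuits. A seed time series taken from infarcted tissue is not a measure of pre-SMA connectivity. It would enter the group-by-time analysis and the Pearson correlations between connectivity change and behavioural gain. A few outlying values carry weight in those correlations at 20 participants per arm.

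**Working it through.** The plan states no figure on this point, so there is none to reproduce. The check follows one hypothetical participant through the stated steps, then bounds what the side rule can catch.

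**1. Path of a participant with an infarcted left pre-SMA**

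| Step | What is tested | Does it test the pre-SMA cortex? |
|---|---|---|
| Eligibility | Side, first-ever, single lesion, non-fluent aphasia | No |
| Choice of side | FA ratio of the FAT | Only indirectly, through the tract that ends there |
| Covariates | Lesion volume, lesion–FAT overlap | No |
| Connectivity seed | Fixed 6-mm sphere | No |

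**2. How far the side rule can act as a safeguard**

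Inputs: in the targeting pipeline (pBFS mapping and white matter reconstruction) streamlines stop at FA < 0.25. In the analysis pipeline (Diffusion data analysis) they stop at FA < 0.2. The cut-off is rFA = 0.5.

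Assume that the mean FA along a traced FAT is at least the stopping value. Then:

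lowest attainable rFA = stopping value / contralesional FA.

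For rFA to reach 0.5 or less, contralesional FA must be at least:

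- 0.25 / 0.5 = 0.50 (targeting pipeline)
- 0.20 / 0.5 = 0.40 (analysis pipeline)

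The documents give no contralesional FA. Over an assumed range of 0.35 to 0.55:

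| Contralesional FA (assumed) | Lowest rFA, stop at 0.25 | Lowest rFA, stop at 0.20 |
|---|---|---|
| 0.35 | 0.71 | 0.57 |
| 0.40 | 0.63 | 0.50 |
| 0.45 | 0.56 | 0.44 |
| 0.50 | 0.50 | 0.40 |
| 0.55 | 0.45 | 0.36 |

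With the targeting pipeline's stopping value, any traceable FAT exceeds 0.5 when contralesional FA is below 0.50. A damaged but traceable tract can therefore be classed as high integrity and the participant kept on the ipsilesional side. If no left FAT can be traced, the ratio is undefined.

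**3. How likely is at least one affected participant?**

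The share p with an infarcted left pre-SMA is not given. The chance of at least one among 40 is 1 − (1 − p)^40:

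| p (assumed) | Expected number | Chance of at least one |
|---|---|---|
| 1% | 0.4 | 33% |
| 2% | 0.8 | 55% |
| 5% | 2 | 87% |
| 10% | 4 | 98.5% |

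These figures concern the seed, which is read whichever side is stimulated.

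**4. Size on the primary outcome**

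Let q be the share of the active arm with an infarcted left pre-SMA, rFA above 0.5 and no benefit. The planned effect of 0.5 becomes 0.5 × (1 − q). One of 20 gives 0.475, two give 0.45 and four give 0.40. Since q counts only those whom the side rule leaves on the ipsilesional side, it should be smaller than p. The upper figures are therefore unlikely.

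**The case against.** The strongest reply is that the trial has a safeguard. The left FAT joins the left pre-SMA to the pars opercularis. An infarct that destroys the left pre-SMA would be expected to disrupt that tract, and stimulation then moves to the right. A reader might infer from the open criteria that any patient with a destroyed left pre-SMA receives iTBS over dead tissue, and that nothing later intervenes. The documents do not support that. The side rule exists for low structural reserve, and a patient moved to the contralesional side is within the stated hypothesis. What remains is the narrower case of damaged cortex with a traceable tract. The bound in the working shows that it is possible, not how common it is.

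A reader might also infer that the choice of target depends on middle cerebral artery sparing, so that enrolment contradicts the rationale. That too is stronger than the text. The Introduction also cites compensatory activation, prediction of recovery and a role in speech initiation and verb generation. Restricting enrolment to middle cerebral artery infarcts would not guarantee sparing, since the claim is only that it is frequent. A restriction of that kind, or a blanket exclusion for left pre-SMA damage, could also remove patients for whom the contralesional option is meant.

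Finally, this is a condensed article. Targeting follows steps set out in Figure 2, whose content was not available for this review, and localisation uses each patient's own connectivity. A lesion check may exist there or in a fuller document. That limits the point to what is stated. The article does, however, define the seed by fixed coordinates and name its lesion covariates, and neither provides a check.

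**Conclusion.** The point holds in a limited form. Followed as written, the plan allows the ipsilesional seed to lie in infarcted tissue and, in a narrower set of patients, the stimulation target as well. The seed problem is the firmer of the two because it does not depend on the side rule, and it bears on the second primary objective. Adjusting for lesion volume and lesion–FAT overlap does not repair a seed signal drawn from the infarct.

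The effect on WAB-AQ is probably small: a 5% relative loss for each affected active participant among 20, and only if that participant gains nothing. The number affected cannot be derived from the documents. The prevalences, the contralesional FA range and the floor on mean tract FA are all assumptions. The change is worth making because it is cheap, not because a large bias has been shown.

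**What to change.** 1. **Settle the order of events first.** Table 1 puts randomisation at Day −7 to −1 and MRI at Day 0, whereas Blinding has randomisation performed once individual targets are determined. A check before allocation is possible only under the second order, so the two must be reconciled.
2. **Check the target.** Before allocation, compute the overlap of each participant's lesion mask with the individual pre-SMA parcel on the assigned side. Reconcile the Introduction, Participants and recruitment, and Personalized stimulation target localization on whether a participant with an infarcted target is eligible. That decision is the sponsor's.
3. **Check the seed.** In the connectivity analysis, remove lesioned voxels from the seed, and drop a participant's maps for that seed when it is largely infarcted. Fix the overlap limit in advance and base it on the baseline mask, so that the exclusion cannot depend on treatment. Report the number affected by arm.

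The cost is an overlap calculation on masks and parcels already produced, and the possible loss of a few candidates or seed maps. Dropping a seed map need not remove the participant from the behavioural analyses.
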